## Abstract

**Aims:**

Bone and joint infections (BJI) in children are rare but can be serious. Differentiating BJI from other conditions with similar symptoms is critical. Advanced imaging (ultrasound scans (USS) and MRI) is often required to confirm the diagnosis. The differing merits of imaging type and regional variation in access to advanced imaging can lead to diagnostic uncertainty and treatment variation. The aim of this study is to evaluate the diagnostic accuracy of MRI and USS for the investigation of BJI in children, and develop and validate prediction models to aid the diagnosis of BJI in children. A nested qualitative sub-study will explore acceptability of the imaging to children, parents, and health practitioners.

**Methods:**

A multicentre retrospective cohort of children (aged < 16 years) with suspected diagnosis of BJI will be used to estimate the diagnostic accuracy of the two imaging methods and develop the prediction models. The models will be evaluated in a second cohort of prospectively recruited children. Diagnostic test accuracy will be estimated overall, and separately for children aged under and over five years. The prediction models will be fit using logistic regression, with candidate predictors chosen based on clinical plausibility and from a review of the literature. Continuous predictors will be examined for non-linearity with confirmed BJI using fractional polynomials. Multiple imputation will be used to replace missing values. Internal validation will be carried out using bootstrapping. Model performance will be assessed with discrimination and calibration.

**Discussion:**

Ethical approval for this study (registration: ISRCTN15471635) was granted (REC reference 23/WM/0027). Informed consent is being obtained from participants in the prospective cohort and the qualitative sub-study. Study findings will be published in an open access journal and presented at relevant national and international conferences. Relevant charities and associations are being engaged to promote awareness of the project.

Cite this article: *Bone Jt Open* 2025;6(6):677–684.

## Introduction

Osteomyelitis is a bacterial infection of bone. In children, it is typically introduced through the blood (haematogenous). Acute osteomyelitis presents with symptoms of less than two weeks’ duration, including pain, loss of limb function, raised temperature, and malaise. The infection frequently ‘breaks out’ into the adjacent joint, causing ‘septic arthritis’, although joint sepsis can also be haematogenous.^1^ Osteomyelitis and septic arthritis in children are inextricably linked and considered together as ‘osteoarticular infection’ or bone and/or joint infection. The burden of bone and joint infection is significant, with data suggesting that approximately 1,800 children (aged 0 to 16 years) are admitted to hospitals in England each year.^2^ Untreated bone and joint infection rapidly progresses to irreversible joint cartilage and/or growth plate damage and bone destruction, leading to a limb-threatening situation, while systemic sepsis can have life-threatening implications. Early differentiation of bone and joint infection from less urgent conditions mimicking the symptoms, such as transient synovitis, is critical.

Clinical work-up typically includes the history of the illness, clinical examination, routine blood tests, and radiographs. However, despite this work-up, clinicians are frequently left facing difficulties in distinguishing bone and joint infection from the other potential causes, and therefore consider advanced imaging. Such imaging includes ultrasound scan (USS) and MRI. USS is more readily accessible and can identify organized fluid collections within joints or tissues, but the overall diagnostic value is unknown. MRI is the gold-standard investigation to diagnose bone and joint infection in adults,^3^ but its diagnostic value is unknown in children. Furthermore, MRI often requires sedation or anaesthesia in children, which influences clinical decision-making.

A clear pathway outlining which tests to perform, and when they are needed, would help to ensure that bone infections are not missed. This would also reduce unnecessary tests in children who do not have an infection and get to a diagnosis more quickly. A recent comprehensive review, through a Health Technology Assessment, concerning advanced imaging for bone and joint infection did not identify any studies of relevance to children.^3^ The Paediatric Emergency Medicine Collaborative in the UK and Ireland (PERUKI)^4,5^ and the Australian Paediatric Emergency Medicine Research Collaborative^6^ have prioritized improving decision support tools, to help differentiate bone and joint infection from other diagnoses, among their top ten most important research areas. In particular, better guidance regarding the use of imaging to optimize the diagnosis of bone and joint infection in children would be valued by clinicians and families.^6-8^

The aim of this study is to evaluate the diagnostic accuracy of MRI and ultrasound scans for the investigation of bone and joint infection in children, and to develop and validate two prediction models (one for children aged under five years, and one for children aged five years and older) to aid the diagnosis of bone and joint infection in children. The prediction models will be developed on the basis of retrospective data of children investigated for infection. They will then be validated on a prospective cohort of children undergoing investigations for bone and joint infection.

## Methods and analysis

### Design

The study will consist of two phases:

A multicentre retrospective cohort study based on hospital records to establish the diagnostic accuracy of MRI and USS, and to develop a clinical prediction model to better inform the diagnosis of bone and joint infection; andA multicentre prospective cohort study to externally validate the clinical prediction model.

In parallel, a qualitative study will aim to inform the management of patients being investigated for bone and joint infection osteomyelitis, including how best to address their information needs and how to support them during the diagnostic process.

The selection criteria and data collection are nearly identical in both the retrospective and prospective cohorts. We have established the feasibility of reliable retrospective data collection through a pilot study.

### Study population

The target population is children and young people aged under 15 years and nine months (aged under 16 years at the end of the three-month follow-up) with a suspected diagnosis of bone and joint infection by the treating clinician. The cohort study will be conducted in NHS secondary care hospitals throughout the UK. The first cohort (retrospective) will be identified through emergency department (ED) records in participating centres. The second cohort (prospective) will also be recruited in ED or acute wards at the same centres. Support from PERUKI and the British Society for Children’s Orthopaedic Surgery (BSCOS)^9^ will help facilitate recruitment and support the study.

We have considered the Innovations in Clinical Trial Design and Delivery for the Under-served (INCLUDE) guidance in preparing the study.^10^ Diversity is particularly important, as diseases which appear more frequently in different racial or ethnic groups may affect the diagnostic process of bone and joint infection (e.g. sickle cell disease, haemophilia). Furthermore, there is evidence that the incidence of bone and joint infection increases with increasing socioeconomic deprivation.^11^ In discussion with our Patient and Public Involvement co-investigators, we will be targeting hospitals covering under-served and ethnically and racially diverse areas (e.g. East London, Birmingham) to ensure our sample is inclusive.

The main inclusion and exclusion criteria for the trial are summarized in Table I.

**Table I. T1:** Inclusion and exclusion criteria.

Inclusion criteria	Exclusion criteria
Age 0 to 15 years	There is evidence that the patient and/or parent/guardian would be unable to adhere to study procedures or complete follow-up
Bone and joint infection is part of the differential diagnosis, even if the treating clinician believes it can be ruled out on the basis of history and examination alone	Limited comprehension by the parent/guardian of the English language
Duration of symptoms < two weeks at the time of attendance to acute healthcare	Suspected infections affecting the axial skeleton (skull, spine, or ribs)
Symptoms affecting the appendicular skeleton only	Traumatic aetiology of symptoms

We have established the feasibility of reliable retrospective data collection through a pilot study.

### Reference standard for diagnosis of bone and joint infection

This is based on a previous large National Institute for Health and Care Research (NIHR)-funded cohort study (DINOSAUR)^7^ and a NIHR-funded Health Technology Assessment of osteomyelitis imaging.^3^ However, several scenarios exist where the prior published reports may not fully inform the reference standard in the context of the current study. To address these gaps, the study management group predefined additional rules, informed by literature, notably:

Conventional radiographs are initially normal in more than 50% of children with osteomyelitis,^7^ although radiological changes typically become apparent within seven to ten days of bacterial joint infection.^12^Spontaneous resolution of bone and joint infection is exceedingly rare, meaning that symptom resolution without antibiotic therapy or surgical intervention would effectively rule out bone and joint infection.^13^

Based on these considerations, the definitive rules for defining bone and joint infection were:

Definitive diagnosis of bone and joint infection, including:

Positive polymerase chain reaction (PCR) joint aspirate; and/orPositive histopathology or microbiology on bone/joint specimen; and/orPositive blood culture with no other source of infection; and/orJoint aspirate > 50,000 white blood cells (WBCs); and/orEvidence of bone and joint infection on two imaging methods or on follow-up imaging.

Definitive exclusion of bone and joint infection, including:

Clinical resolution of symptoms without antibiotic treatment by three months. Less than 24 hours of treatment dose antibiotics is considered as ‘no’ antibiotic use; and/orConfirmation of an alternative diagnosis to explain symptoms subsequently established.

Uncertain group, including:

Children with negative or equivocal diagnostic investigations – recovered following more than 24 hours of antibiotic treatment.

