### Sample size considerations

Sample size for retrospective cohort to estimate the diagnostic accuracy: For the primary objective, we will collect retrospective data for an estimated sample of 6,000 children with suspected bone and joint infection. Based on our feasibility data, approximately 444 (7.4%) would have confirmed bone and joint infection and 5,556 (92.6%) would be disease-free. Based on our pilot study, this would provide data for approximately 351 (79%) MRI disease cases and 408 (92%) USS disease cases, allowing MRI sensitivity to be estimated to within 2.9 percentage points of 91.5% and USS sensitivity to be estimated to within 4.3 percentage points of 74.1% with 95% confidence. This would also provide 611 (11%) MRI and 1,000 (18%) USS disease-free cases, allowing specificity to be estimated to within 3.7 percentage points of 67% for MRI and within 3.1 percentage points of 47% for USS with 95% CI.

Sample size for retrospective cohort to develop the diagnostic prediction model: We will develop two diagnostic prediction models to predict bone and joint infection; one for children aged under five years (Model 1) and one for children aged five years and older (Model 2).

In the retrospective cohort, we anticipate that there will be 1,440 children aged under five years, of whom 107 have a bone and joint infection for Model 1, and 4,560 children aged five years and older, of whom 348 have a bone and joint infection for Model 2. This is based on the estimate that 24% of children with confirmed bone and joint infection will be aged under five years (NHS Digital 2017/18).^14^

Using this information and to minimize the risk of overfitting and to precisely estimate the overall outcome risk, we calculated that ten predictors can be examined for inclusion in Model 1 and 32 predictors can be examined for inclusion in Model 2. This is based on a conservative estimate of the anticipated R^2^ of 0.15*max(R^2^) (max R^2^ = 0.41 for an anticipated outcome prevalence of 0.074).^15^

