### Statistical analysis

Diagnostic test accuracy: For each index test (USS and MRI), the results will be compared to the reference standard among all patients with available data and cross tabulations reported (including indeterminate results). The sensitivity, specificity, negative predictive value, positive predictive value, likelihood ratio, and diagnostic odds ratios will be reported (with 95% CIs) overall, as well as separately for patients aged five years and older versus those aged under five years. This choice was based on our feasibility study finding that most children under the age of five years require sedation or anaesthesia for MRI, while those aged five years and above do not.

Model development and validation: Two models will be fitted using logistic regression: one for children aged under five years and one for children aged five years and older. A single unified model will also be explored. Candidate predictors for both models will be chosen based on clinical plausibility and from a review of the literature. We will select variables for inclusion in the model using least angle selection and shrinkage operator (LASSO) penalties. Continuous predictors will be examined for nonlinear relationship with confirmed bone and joint infection using fractional polynomials.^18^ Missing data will be inevitable with not all patients providing data on all predictors of interest.

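### The reference standard has an uncertain group, but the planning figures leave no room for it, and its wording does not clearly place a treated child with one positive scan

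*Protocol article*

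**What the plan says.** In the protocol article, 'Reference standard for diagnosis of bone and joint infection' sets out three groups.

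- **Definite infection:** any one of several microbiological, histological or aspirate criteria, or imaging evidence on two methods or on follow-up imaging.
- **Definite exclusion:** symptoms resolved by three months without antibiotics (under 24 hours counts as none), or an alternative diagnosis was confirmed.
- **Uncertain:** "Children with negative or equivocal diagnostic investigations" who recovered after more than 24 hours of antibiotics.

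'Sample size considerations' starts from everyone under suspicion: "we will collect retrospective data for an estimated sample of 6,000 children with suspected bone and joint infection". It then uses two groups: "approximately 444 (7.4%) would have confirmed bone and joint infection and 5,556 (92.6%) would be disease-free". The specificity denominators are shares of the second number: "611 (11%) MRI and 1,000 (18%) USS disease-free cases". The update of October 2024 gives 180 infections among 3,426 younger children and 177 among 2,314 older children, with no count of uncertain children in either.

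'Statistical analysis' compares each scan with the reference standard in all patients with available data and promises cross tabulations that include indeterminate results. The models are binary logistic regressions. The outcome is named in one sentence: "Continuous predictors will be examined for nonlinear relationship with confirmed bone and joint infection using fractional polynomials".

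**The concern.** Under the protocol's own rule, a child treated for more than 24 hours without an alternative diagnosis cannot be called free of infection. The planning figures nevertheless give that label to every child who is not confirmed. The 611 and 1,000 are therefore not counts of definitively excluded children, and the stated specificity precision belongs to a mixed group.

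The rules also leave a gap. Take a child with one positive imaging method, no other definite criterion and no alternative diagnosis, who was treated for more than 24 hours and recovered. The child is not definite, because two methods or follow-up imaging are needed, and is not excluded, because of the treatment. Nor is the child uncertain as worded, because one investigation was positive.

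Such a child has a positive scan on one of the tests being evaluated, so the placement feeds directly into the study's main estimates. If these children and the uncertain group are kept as non-cases, specificity is measured partly in possibly infected, treated children, and the models learn from the same mixture.

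**Working it through.** **Inputs from 'Sample size considerations'.** 6,000 children; 444 confirmed and 5,556 disease-free; 351 disease cases with MRI at sensitivity 91.5%; 611 disease-free children with MRI at specificity 67%; 1,000 with USS at 47%; updated counts 180/3,426 and 177/2,314.

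**Reproducing the plan.**
- 6,000 × 0.074 = 444 and 6,000 − 444 = 5,556. The sum is 6,000, so the planned uncertain share is 0%.
- 0.11 × 5,556 = 611 and 0.18 × 5,556 = 1,000.
- Half-width = 1.96 × √(p(1−p)/n). MRI specificity: 1.96 × √(0.67 × 0.33/611) = 3.73 points. USS specificity: 1.96 × √(0.47 × 0.53/1,000) = 3.09 points. Both agree with the plan: "specificity to be estimated to within 3.7 percentage points of 67% for MRI and within 3.1 percentage points of 47% for USS".
- 180/3,426 = 5.3% and 177/2,314 = 7.6%. The other 3,246 and 2,137 children are not split into excluded and uncertain.

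**Effect on the specificity estimate.** The number of uncertain or unplaced children is not given. Assume 2-5% of 6,000 (120-300), half of them with MRI (a = 60-150). They already sit inside the 611, so the check removes them. It takes the 67% as computed with them included, which the protocol does not state. With s the share that is scan-positive, specificity after removal is (0.67 × 611 − (1−s)a)/(611 − a), and 0.67 × 611 = 409.4.

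| Scan-positive share s | a = 60 (n = 551) | a = 150 (n = 461) |
|---|---|---|
| 0 (all negative) | 349.4/551 = 63.4% | 259.4/461 = 56.3% |
| 0.5 | 379.4/551 = 68.9% | 334.4/461 = 72.5% |
| 1 (all positive) | 409.4/551 = 74.3% | 409.4/461 = 88.8% |

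At s = 0.5 the shift is 1.9 to 5.5 points, and only the upper part exceeds 3.7. The sign turns at s = 0.33. The uncertain group as worded would tend towards scan-negative, and the unplaced children towards scan-positive, so the direction depends on the mix.

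**The opposite bound.** If the same children were all counted as infected, with s = 0.5, MRI sensitivity would be (0.915 × 351 + 0.5a)/(351 + a). This gives 351.2/411 = 85.4% for a = 60 and 396.2/501 = 79.1% for a = 150, against 91.5% ± 2.9.

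**Effect on precision.** Hold specificity at 67% and remove the uncertain children, with 11% to 79% of them having MRI (the plan's own MRI shares in disease-free and diseased children).
- 2% uncertain: 120 × 0.11 = 13 to 120 × 0.79 = 95 removed; 598 to 516 remain; half-width 3.8 to 4.1 points.
- 5% uncertain: 300 × 0.11 = 33 to 300 × 0.79 = 237 removed; 578 to 374 remain; half-width 3.8 to 4.8 points.

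**Effect on the models.** Removing 2-10% of each updated cohort raises prevalence to 5.4-5.8% (180 divided by 98% to 90% of 3,426) and 7.8-8.5% (177 divided by 98% to 90% of 2,314). The predictor limit, n × (−0.1) × ln(1 − R²/0.9) with R² = 0.15 × max R², becomes 19.7-19.0 for Model 1 and 16.5-15.9 for Model 2, against the stated 19 and 16. The limits barely move.

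**The case against.** The 444/5,556 split is an approximate planning figure from feasibility data, not an analysis rule. The article is abridged and points to a full working protocol, and how uncertain children enter the tables and models is commonly settled there or in an analysis plan. The promised indeterminate results might already mean a separate reference-standard row. Each of the three group lists is introduced as including its items, so a treated child with one positive scan could be read into the uncertain group. Dropping uncertain children is not neutral either, since it removes the hardest cases.

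Much of this stands. A reader might infer that the analysis will code uncertain children as non-cases. No passage says so: the outcome name appears in a sentence about fractional polynomials and does not define the comparison group. A reader might also infer that specificity is biased downwards, that model coefficients are pulled towards the null, or that the single-positive-scan pattern is common. The documents support none of these: the group's size, scan results and true infection share are not given, and the sign of the specificity shift changes with the scan-positive share.

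The contradiction between stated figures remains. The 6,000 are all suspected children, the exclusion rule shuts out treated children without an alternative diagnosis, and the 5,556 let them in. It persists in the update, which used records already collected. An open-ended list still gives no rule for the child described, and the text does not say whether indeterminate refers to the scan or to the reference standard.

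**Conclusion.** The point holds as a contradiction within the protocol and a gap in its classification wording. The three-group reference standard and the two-group planning totals must be reconciled, and every child needs a stated group.

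The consequence for the results is conditional: bias arises only if these children are analysed as non-cases, and its size and direction cannot be derived from the documents. Under the assumed 60 to 150 affected children with MRI, half scan-positive, removing them shifts MRI specificity by 1.9 to 5.5 points against a planned 3.7. Other scan-positive shares give larger shifts or the opposite sign. The predictor limits are hardly affected. The change should be made, because the reference standard underlies both the accuracy estimates and the models.

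**What to change.** 1. For analysis, assign every child who meets neither the definite nor the exclusion criteria to the uncertain group, including the treated child with one positive imaging method. The same rule would cover children whose three-month status is unknown.
2. Restate the disease-free counts, the MRI and USS specificity precision and the two prevalences, with non-cases limited to definitively excluded children. Give the uncertain count for each age group.
3. Show the uncertain group as a separate reference-standard row in each cross tabulation, by scan and age group, distinct from indeterminate scan results.
4. Report accuracy and model results with two bounding analyses, one with all uncertain children as infected and one with all as disease-free, since leaving them out is not neutral.

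The cost is a wording change and two further analyses on data already being collected. Definite-versus-excluded estimates will have fewer non-cases and a wider specificity interval, for example ±3.8 to 4.8 points for MRI if 2-5% of the cohort is uncertain. The rewording would come after retrospective collection began, so it should be dated and made before the accuracy results are seen.

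### MRI and USS help to define a confirmed case in the standard they are tested against, so their sensitivity is probably overstated, more clearly for USS, by an unknown amount

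*Protocol article*

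**What the plan says.** In the protocol article, the section on the reference standard sets up three groups.

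- **Definitive infection.** Any one criterion is enough. Four are laboratory criteria: PCR on a joint aspirate, histopathology or microbiology of a specimen, an otherwise unexplained positive blood culture, and a high aspirate white cell count. The fifth is imaging: signs of infection on two modalities, or on later imaging.
- **Definitive exclusion.** "Clinical resolution of symptoms without antibiotic treatment by three months", or a confirmed alternative diagnosis.
- **Uncertain.** "Children with negative or equivocal diagnostic investigations" who got better after antibiotics given for longer than 24 hours.

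Under Statistical analysis, the accuracy paragraph states: "For each index test (USS and MRI), the results will be compared to the reference standard among all patients with available data". Cross-tabulations are to include indeterminate results. The paragraph does not say how the uncertain reference group enters the calculation.

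Under Sample size considerations, the whole planned sample of 6,000 is divided in two: "approximately 444 (7.4%) would have confirmed bone and joint infection and 5,556 (92.6%) would be disease-free". The sensitivity denominators come from the first part, as "approximately 351 (79%) MRI disease cases and 408 (92%) USS disease cases". The precision claim is "allowing MRI sensitivity to be estimated to within 2.9 percentage points of 91.5" percent for MRI, and 4.3 points around 74.1% for USS.

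**The concern.** The index tests take part in deciding who is a case. Consider an infected child whom no laboratory criterion confirms. If two imaging modalities are positive, the child is a definitive case. If the investigations are negative or equivocal and the child recovers on antibiotics, the child is uncertain and is not among the confirmed cases behind the sensitivity figures. In this stratum, entry to the denominator depends on the results being evaluated, and positive scans are favoured.

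Sensitivity belongs to the primary objective. It determines how far a negative scan can be trusted, in a condition the Introduction describes as limb-threatening when untreated. The confidence intervals reflect sampling error only, and more children would not remove a selection effect of this kind.

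**Working it through.** **1. The plan's own precision.** Half-width = 1.96 × √(p(1−p)/n), with inputs from Sample size considerations.

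- MRI: 1.96 × √(0.915 × 0.085 / 351) = 2.9 points (stated 2.9).
- USS: 1.96 × √(0.741 × 0.259 / 408) = 4.3 points (stated 4.3).

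Both reproduce. The question is bias, not arithmetic. Also, 444 + 5,556 = 6,000, so the planning figures leave no room for an uncertain group.

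**2. How few children matter.** Let u be the number of infected, scan-negative children left in the uncertain group. Sensitivity with them restored = p × n / (n + u). The values of u are hypothetical.

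| Test | u | Calculation | Result |
|---|---|---|---|
| MRI | 12 | 0.915 × 351 / 363 | 88.5% |
| MRI | 18 | 0.915 × 351 / 369 | 87.0% |
| MRI | 35 | 0.915 × 351 / 386 | 83.2% |
| USS | 25 | 0.741 × 408 / 433 | 69.8% |

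About 12 such children for MRI, or 25 for USS, shift the estimate by roughly the whole planned half-width.

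**3. Direction under the stated rules.** Assumptions, none of them from the article:

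- MRI, USS and radiograph are all done and are independent given infection.
- A share m of infections is confirmed without imaging.
- The rest count if at least two of the three images are positive, or if follow-up imaging captures them. Otherwise they are uncertain.

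Apparent sensitivity = P(test positive and counted) / P(counted).

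One case in full: true MRI 85%, true USS 65%, radiograph 30%, m = 0.5.

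- P(MRI+ and USS+) = 0.85 × 0.65 = 0.5525
- P(MRI+, USS−, radiograph+) = 0.85 × 0.35 × 0.30 = 0.0893
- P(MRI−, USS+, radiograph+) = 0.15 × 0.65 × 0.30 = 0.0293
- P(two or more positive) = 0.671; with MRI positive 0.6418; with USS positive 0.5818
- P(counted) = 0.5 + 0.5 × 0.671 = 0.8355
- Apparent MRI = (0.5 × 0.85 + 0.5 × 0.6418) / 0.8355 = 89.3%
- Apparent USS = (0.5 × 0.65 + 0.5 × 0.5818) / 0.8355 = 73.7%

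**4. Adding the follow-up imaging route.** Same true values (85% and 65%), with the radiograph at 20–40% and m at 0.3–0.7.

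| Follow-up imaging captures | Apparent MRI (true 85%) | Apparent USS (true 65%) |
|---|---|---|
| nobody | 87–92% | 69–80% |
| half of the remainder | 86–88% | 67–72% |
| 80–100% of MRI-negative children only | 82–85% | 69–78% |

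USS is overstated in every row. The MRI shift shrinks to about 1–3 points in the second row, and vanishes or reverses in the third.

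**5. Starting from the plan's own values.** Take 91.5% and 74.1% as true, the radiograph at 30–45%, m at 0.4–0.8, and follow-up imaging capturing 0–50% of the remainder without regard to the MRI result. Apparent MRI is then 91.9–94.7% and apparent USS 75.2–83.0%. The upward shift is 0.4–3.2 points for MRI and 1.1–8.9 points for USS.

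**The case against.** Several points against this carry weight.

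- **Not every false negative is lost.** A reader might infer that, without laboratory confirmation, every true-positive scan is counted and every false-negative scan is dropped. The text does not support that. A child negative on MRI but positive on USS and radiograph is a case. So is one detected on later imaging, and the article notes that radiographic changes tend to emerge after seven to ten days.
- **The direction for MRI is not certain.** A reader might infer that both sensitivities must be biased upward. If later imaging is aimed at MRI-negative children, the MRI bias can vanish or reverse.
- **One positive scan has no stated place.** The uncertain entry covers negative or equivocal investigations. Treating a child with a single positive scan as uncertain, as the model above does, is an assumption.
- **The figures are illustrations.** The counts of 18 and 35 are not bounds, since the article gives nothing from which to derive them. Having all three images done is also a simplification: the article expects MRI in 79% and USS in 92% of confirmed cases. Starting from the planned 91.5%, most of the modelled MRI range lies within the stated ±2.9 points.
- **The analysis plan may add sensitivity analyses.** The article is abridged, and such detail often sits elsewhere. Indeterminate results are to be cross-tabulated, though the text does not say whether that covers the uncertain reference group.

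What remains is that the case definition is fixed in this article and includes the tests under evaluation. Displaying indeterminate results does not put uncertain children into a sensitivity denominator. Allowing a radiograph as one of the two modalities weakens the bias under the model but does not reverse it.

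**Conclusion.** The point holds as a probable overstatement of sensitivity, of unknown size, more clearly for USS than for MRI. The mechanism follows from the reference standard read together with the accuracy analysis and the planned denominators. The size cannot be derived from the article.

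Under the assumptions above, the USS shift ranges from about 1 point to 15 points (65% appearing as 80%). The MRI shift ranges from about 7 points upward (85% appearing as 92%) to 3 points downward (82%) when follow-up imaging targets MRI-negative children. These ranges rest on conditional independence, on assumed radiograph sensitivity, and on assumed shares confirmed without imaging. The article does not support calling the overstatement certain for both tests.

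**What to change.** In the diagnostic accuracy paragraph of Statistical analysis, report beside the main estimate, for each test:

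1. Sensitivity among cases confirmed by a non-imaging criterion (PCR, histopathology or microbiology, blood culture, or aspirate count).
2. A worst-case sensitivity with the uncertain group counted as infected, labelled as an extreme lower bound because some of these children were not infected.

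State that the main sensitivity applies to confirmed infection as defined, with imaging part of that definition, and interpret any rule-out conclusion in the light of these analyses. In the reference standard section, state where a child with a single positive scan and no other confirmation belongs.

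The cost is two extra rows per test from data already collected, and a few sentences. The downsides are:

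- Analysis 1 is less precise. If half of the 351 MRI cases qualify (about 176), the half-width is 1.96 × √(0.915 × 0.085 / 176) = 4.1 points instead of 2.9.
- Analysis 1 is not wholly free of selection, because an aspiration may be prompted by a positive scan.
- The bound in analysis 2 may be too wide to be informative if many uncertain children were treated as a precaution.
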